## Justification of 0, 1, & 2 Month Dosing

Most previous FMP-1 studies have been conducted using a 0, 1, and 3 month immunization schedule. Our previous phase I trial in 40 adults in Kombewa District, Kenya used a 0, 1, and 2 month schedule. Our overall FMP-1 testing program, although initially directed at adults, aims ultimately at evaluating the vaccine in children. With this goal in mind, the more accelerated schedule anticipates that such intervals will ultimately be more amenable to incorporation into the World Health Organization’s Expanded Program of Immunizations (EPI).

For justification of the 0, 1, and 2 month dosing of the comparator vaccine, see Section 4.7.2.

## Comparison Vaccine

### **The Vaccine**

A rabies vaccine (Imovax® Rabies vaccine) will serve as the comparator in this study. Imovax® is produced by Aventis Pasteur, SA and the recommended doses and schedules are the same for infants, children and adults. (See Section 10.2 for more details.) Rabies vaccine is a parenteral preparation of inactivated rabies virus used to promote active immunity to rabies in individuals exposed to the disease or virus. Prophylactic doses of rabies vaccine are administered to certain groups of people at high-risk for acquiring rabies infection. Advantages of providing preexposure vaccination include reduced number of doses of the vaccine after a rabies exposure, elimination of need for rabies immune globulin postexposure, possible protection in persons whose post-exposure therapy is delayed or unavailable, and possible protection for persons at risk for inapparent exposures to rabies. Preexposure vaccine is recommended for individuals who are at risk of occupational exposure to the rabies virus (e.g., physicians, veterinarians, laboratory workers, animal handlers). Preexposure vaccination is also recommended for other persons whose activities involve frequent contact with rabies virus or potentially rabid animals such as bats, raccoons, skunks, cats, dogs, or other species at risk for having rabies. Preexposure vaccination is commonly recommended in international travelers who are likely to come in contact with animals in areas where dog rabies is enzootic and immediate access to appropriate medical care, including biologics, might be limited.

Receipt of Imovax® is expected to benefit this population of children as rabies is prev-alent throughout Kenya and is a particular concern in children subjected to dog bites. The investigators have elected to use rabies vaccine over hepatitis B vaccine as the comparat-or. A hepatitis B vaccine was recently introduced into western Kenya as part of the Kenya Expanded Programme on Immunizations (KEPI) and the investigators are aware that most of the Kombewa children now 12-24 months of age have received it. Rabies is prevalent throughout Kenya due to the presence of many unvaccinated dogs (24). There-fore, the investigators believe that rabies immunization may be more beneficial to this local population.

Although only the 45 comparison subjects will receive this comparator vaccine during the active phase of the study, it will also be offered free of charge to the remaining 90 children after study completion.

### **Vaccine Immunogenicity**

When Imovax® is administered according to the recommended immunization schedule (days 0, 7, 21), nearly 100% of subjects attain a protective titer. In two studies carried out in the US in 101 subjects, antibody titers > 0.5 IU/ml were obtained by day 28 in all subjects. In studies carried out in Thailand in 22 subjects, and in Croatia in 25 subjects, antibody titers of > 0.5 IU/ml were obtained by day 14 (injections on days 0, 7, 21) in all subjects (25-29). High antibody titers have also been demonstrated with off-label immunization with Imovax Rabies. Among participants in England, Germany, France and Belgium who received two doses one month apart, nearly 100% of the participants developed specific antibody and the geometric mean titer for the group was 10 IU (30-33). The proposed immunization schedule of 0, 1, and 2 months is therefore expected to be highly successful in conferring protective immunity against rabies among the control participants.

### **Vaccine Safety**

Both safety and efficacy have been established for Imovax® Rabies vaccine in children. Local and/or mild systemic reactions may occur after injection, but these are usually transient and do not contraindicate continuing immunization. Imovax® is a human diploid cell vaccine (HDCV). In a study using 5 doses of HDCV, local reactions such as pain, erythema, and swelling or itching at the injection site were reported in about 25% of recipients (35).Mild systemic reactions such as headache, nausea, abdominal pain, muscle aches, and dizziness were reported in about 20% of recipients (35). Two cases of neurologic illness resembling Guillan-Barre syndrome, a transient neuroparalytic illness, and a focal subacute central nervous system disorder temporally associated with HDCV have been reported (36-38).

Systemic allergic reactions characterized by generalized urticaria and in some cases by arthralgia, angioedema, fever, nausea and vomiting have been reported following administration of HDCV. These reactions are uncommon in primary administrations but have been reported in up to 7% of persons receiving a booster dose (39).

## Malaria in Western Kenya

Malaria in western Kenya is holoendemic. Intense transmission occurs primarily by bites of the *Anopheles gambiae* mosquito. *P. falciparum* parasitemia is present in over 90% of malaria cases. *P. ovale* and *P. malariae* together constitute less than 10% and are usually present in mixed infections with *P. falciparum.* Malaria transmission occurs all year but at a very high level during the two rainy seasons. The “long rainy season”of late March through May, produces intense transmission from April through August; the “short rainy season” of October through December produces another, somewhat less intense, transmission season from November through January. The intensity of both of these transmission seasons can be predicted by the amount of rain seen in the preceding month and correlates with both the total population of female anopheline mosquitoes and the entomological inoculation rate (EIR, i.e., the number of infected mosquito bites per person per day). Cumulative malaria attack rates have been in the order of 95% during the long rains and 75% during the short rains. The adult population of several villages not far from the study site has been subject of several malaria chemotherapy and epidemi-ology studies. These studies typically demonstrate about 90% incidence of parasitemia over 12 weeks during a high transmission period. Approximately 25% of these infected adults will become symptomatic at some time during that period. A large-scale longitud-inal cohort project recently undertaken in Kisumu District (Bloland PB, Boriga DA, Ruebush TK, et al, “Longitudinal cohort study of the epidemiology of malaria infections in an area of intense malaria transmission II. Descriptive epidemiology of malaria infection and disease among children.” *Am J Trop Med* *Hyg* 1999 Apr; 60(4):641-8) documented, over the course of two disease seasons, that the malaria parasite prevalence in the proposed study district and in the proposed study age groups (1-4 year olds) was 83%. All individuals in this population are parasitemic multiple times over a lifetime. There is no doubt whatever that children in this population are “malaria-exposed”.

The Walter Reed Project (WRP) and the Kenya Medical Research Institute (KEMRI) have been involved in malaria research in western Kenya for many years. These studies cover nearly every aspect of the disease: epidemiology, entomology, immunology, hospital-based treatment trials, and community-based studies of antimalarials. The WRP/KEMRI laboratories near Kisumu have served as the base for both phase I and II trials of candidate malaria vaccines and antimalarial drugs over the past decade. In spite of these research efforts, malaria infections in this area continue unabated and improved control strategies are required.

# JUSTIFICATION

Children are the population with the highest rates of morbidity & mortality due to malaria, accounting for more than 1 million deaths in sub-Saharan Africa. Malaria is a very significant cause of morbidity and mortality in both adults and children in western Kenya. This area is understood to be one in which the burden of malaria falls particularly hard on the younger age groups, thereby making these groups unusually amenable to scientific study. Worldwide, the populations at risk for malaria include not only the infants, children and adults in malaria-endemic regions, but also non-immune travelers to malarious areas including vacationers and deploying military personnel. A safe and effective vaccine that prevented infection, or even merely clinical symptoms, of *P. falcip-arum* malaria would be a milestone public health achievement and would become a mainstay in efforts to control this most serious infectious disease around the world. The increasing prevalence of drug resistance in various malaria strains makes an effective vaccine an international priority in the struggle for control of this devastating disease.

The target population for this particular vaccine is children at risk for clinical disease (including severe disease) due to infection with *P. falciparum*. MSP-1 can only be tested for proof of concept in this population, as there is no predictive animal model and no reliable challenge system to detect efficacy against clinical malaria. This vaccine has been tested in malaria naïve adults (US) to establish safety, reactogenicity and to identify a dose for further evaluation. It was subsequently evaluated in malaria-exposed adults (Kenya) & has been found to be safe, well tolerated & immunogenic in this pop-ulation. The AS02A adjuvant has been tested in combination with the RTS,S vaccine in adults & children aged 1 year & older with prior (and ongoing) exposure to *P. falciparum* malaria. This AS02A-containing vaccine has been found to be safe & well tolerated.

The next logical step in the clinical development of FMP-1/AS02A is its introduct-ion into the pediatric population in a cautious, step-wise manner as described in this protocol.

# OBJECTIVES

## Primary objective

- To assess the safety and reactogenicity of the FMP-1/AS02A malaria vaccine in 12-47 month old, malaria-exposed children living in western Kenya

## Secondary objective

- To assess the humoral immune response to the FMP-1/AS02A malaria vaccine in 12-47 month old, malaria-exposed children living in western Kenya

# STUDY DESIGN & METHODOLOGY

## Overview

- Double blind, randomized, controlled, dose escalation, phase I study of a candidate vaccine/adjuvant
- One study center, with 2 outlying (satellite) field stations
- Screening will be incremental & will be done within 35 days prior to the first inoculation for each cohort.
- 135 subjects will be divided equally among 3 cohorts (1/5, ½ or full dosage groups: 10, 25 or 50 g, respectively) of 30 subjects each and a comparison group of 15 subjects (Total subjects per cohort = 45).
- Each cohort will be stratified byage group (12-23, 24-35, and 36-47 months) (Total subjects in each of 3 age groups [among all cohorts]= 45).
- The comparison groups (total of 45 subjects in all 3 age groups) will receive Imovax® Rabies vaccine.
- Immunization schedule will be 0, 1, and 2 months for all cohorts (Provisionally: Study days 0, 29 and 57 for Cohort A; 14, 42, 70 for Cohort B; and 28, 56, 84 for Cohort C)
- Vaccinations of Cohorts B and C (FMP-1 doses of 25 ug and 50 ug respectively, with control subjects) will be offset (“staggered”): Cohort B following Cohort A by 2 weeks and Cohort C following Cohort B by 2 weeks. These intervals may be extended for up to 5 weeks, however, if *temporary discontinuation* (see Section 7.9.1) is deemed advisable due to SAEs or other concerns.
- Subjects in each cohort will be randomized separately from the other cohorts, at the times of first vaccinations.
- Route of inoculation will be by IM injection into right or left (alternately) antero-lateral thigh muscles (unless compelling reason for an alternate injection site is evident).
- Study duration will be approximately 12 months per subject.
- Seven (7) day follow-up period for solicited adverse events (5 visits: Vaccination day plus days 1, 2, 3 and 7 post-vaccination)
- Thirty (30) day follow-up period for unsolicited adverse events (Vaccination day plus 29 subsequent days)
- Follow-up of serious adverse events (SAE’s) for 8 months after the first dose of study vaccine (6 months after dose 3)
- At the end of the follow-up period for unsolicited AEs (i.e., after the third dose; Study day 90), subjects will be followed by field workers at home at monthly intervals and will be asked to return to clinic every 3 months for long-term clinical and immunogenicity follow-ups.

## Number of Subjects, Number of Study Arms & Number of Study Cohorts

The study will randomize 135 subjects, irrespective of gender, who fulfill all enrollment criteria. These subjects will be recruited into one of 3 cohorts (dosage groups), each containing a total of 45 subjects. Each cohort will be composed of 15 subjects in each of 3 age groups (12-23 months, 24-35 months, and 36-47 months; monthly ages are rounded down, e.g., a child who is 24.5 months old is considered to be 24 months old). Moreover, each cohort will be composed of 30 FMP-1 recipients (either 10 g, 25 g or 50 g) and 15 Imovax® (comparator vaccine) recipients.

Age-stratification will be maintained down to the smallest groups; i.e., an FMP-1 to Imovax® ratio of 10: 5 will be maintained in each age-group of a given cohort. Recruitment of subjects into each age-group of a cohort will be separately incremental (i.e., recruitment will not stop in any age group of a cohort until 15 children have been recruited, randomized, and vaccinated). Recruitment will stop altogether when the total number of subjects enrolled has reached 135.

Cohort A: The 30 subjects receiving 1/5th dose = 10 g of FMP-1 (10 subjects from each of the 3 age groups), plus the 15 subjects receiving the Imovax® comparator (5 subjects from each of the 3 age groups), together constitute Cohort A.

Cohort B: The 30 subjects receiving ½ dose = 25 g of FMP-1 (10 subjects from each of the 3 age groups), plus the 15 subjects receiving the Imovax® comparator (5 subjects from each of the 3 age groups), together constitute Cohort B.

Cohort C: The 30 subjects receiving full dose = 50 g of FMP-1 (10 subjects from each of the 3 age groups), plus the 15 subjects receiving the Imovax® comparator (5 subjects from each of the 3 age groups), together constitute Cohort C.

These age groups, study arms and cohorts are presented in tabular fashion in Tables 2 and 3.

**Table 2: Numbers of Subjects by Cohorts, Study (Dosage) Arms & Age Groups**

|  | **Receiving Test**  **(FMP-1) Vaccine** | | | | **Receiving Comparator (Rabies) Vaccine** | | |
| --- | --- | --- | --- | --- | --- | --- | --- |
| Ages (Months) | **Dose** | 12-23 | 24-35 | 36-47 | 12-23 | 24-35 | 36-47 |
| **Cohort A** | 10 g | 10 | 10 | 10 | 5 | 5 | 5 |
| **Cohort B** | 25 g | 10 | 10 | 10 | 5 | 5 | 5 |
| **Cohort C** | 50 g | 10 | 10 | 10 | 5 | 5 | 5 |
| **Age Group Totals** |  | **30** | **30** | **30** | **15** | **15** | **15** |
| **Vaccine Group Totals** | **90** | | | | **45** | | |
| **Grand Total** | **135** | | | | | | |

**Table 3: Numbers of Subjects by Cohorts & Age Groups**

|  | **Total Vaccinated**  (FMP-1 & Rabies)  in each age group | | | **Totals**  in each cohort |
| --- | --- | --- | --- | --- |
| Ages (Months) | 12-23 | 24-35 | 36-47 | **45**  **45**  **45** |
| **Cohort A** | 15 | 15 | 15 |
| **Cohort B** | 15 | 15 | 15 |
| **Cohort C** | 15 | 15 | 15 |
| **All Cohorts** | **45** | **45** | **45** |
| **Grand Total 135** | | | | |

## Study Center

The Walter Reed Project (WRP) Kombewa Clinic (WRP KC) is located in the village of Kombewa, in Kombewa Division, Kisumu District, Nyanza Province. Kom-bewa Town is about 40 kilometers west of Kisumu Town.

The WRP KC is located directly across the Kombewa-Maseno road (a murram road) from the Kombewa Sub-District Hospital (KSDH) and it is less than 1 kilometer north of the Kisumu-Bondo road (which is macadamized). The KSDH is a Ministry of Health sub-district hospital. It is an outpatient and inpatient facility with a 24-26 bed capacity. The director is a Clinical Officer (physician assistant equivalent) assisted by a team of 9 nurses. The facility is staffed 24 hours/day and has a basic laboratory that can do malaria smears for diagnosis.

The WRP KC, the study center itself, is readily accessible by foot or ground vehicle to all study subjects. It consists of a clinical laboratory equipped to carry out malaria diagnosis and basic clinical laboratory assays (such as measurement of serum chemistries and complete blood counts), a phlebotomy room, an outpatient facility that includes 6 examination/consultation rooms, a pharmacy, an active records room, and an archive. Source documents and CRFs will be kept in locked cabinets in the latter two rooms. Additionally, the facility has a dedicated data entry room, offices for clinical officers and clinical coordinators, on-call rooms, an urgent treatment room, a 4-bed overnight-care ward, a wash room, a general store, and a kitchen with dining facility. The PI, associate investigators, and clinical officers who are experienced clinicians will carry out the clinical evaluations, including laboratory evaluations, in this facility. A clinical staff member will be available there 24 hours/day and 7 days/week during active studies.

## Inclusion Criteria

- A healthy male or female child, 12 to 47 months of age at the time of screening.
- Written informed consent obtained from at least one parent before study start.
- Available to participate for the duration of the study (12 months).

## Exclusion Criteria

**The following criteria should be checked at the time of study entry. If any apply at the time of study entry, the subject must not be included in the study:**

- Acute disease at the time of entry into the study
- Axillary temperature of 37.5C
- Respiratory rate  50
- Serum ALT  45 IU/l (i.e., > 1.5 X ULN)
- Decreased renal function: serum creatinine levels > 92.2 mM/l (> 1.1 mg/dl).
- Significant anemia (Hgb <8 gm/dL).
- Thrombocytopenia (Platelets < 100,000 per mm3)
- Impaired immunity: (Absolute lymphocyte count [ALC] for 1 year olds < 4.0 x 103/mm3; for 2 year olds < 3.0 x 103/mm3; for 3 year olds < 2.0 103/mm3.
- History of homozygous sickle cell disease (SS).
- Malnutrition (Z score; Malnutrition = Weight for height < - 3 z scores)
- Blood transfusion or use of blood-based product in previous 6 months.
- Prior receipt of a rabies vaccine or an investigational malaria vaccine.
- Use of any investigational drug or vaccine other than the study vaccine within 30 days preceding the first dose of study vaccine, or planned use up to 30 days after the third dose.
- Administration of chronic (defined as more than 14 days) immunosuppressants or other immune-modifying drugs within six months of vaccination. (For cortico-steroids, this will mean prednisone, or equivalent, greater than or equal to 0.5 mg/kg/day. Inhaled and topical steroids are allowed).
- Administration or anticipated administration of a vaccine not foreseen by the study protocol within 30 days of the first dose of vaccine(s) with the exception of tetanus toxoid.
- Previous vaccination with a vaccine containing MPL or QS21 (e.g., RTS,S).
- Any confirmed or suspected immunosuppressive or immunodeficient condition, including human immunodeficiency virus (HIV) infection. (No HIV testing will be undertaken as part of this study.)
- History of allergic reactions or anaphylaxis to immunizations or to any vaccine components.
- History of surgical splenectomy.
- Administration of immunoglobulins or any blood products within the 3 months preceding the first dose of study vaccine or planned administration during the study period.
- Simultaneous participation in any other clinical trial.
- Acute or chronic cardiovascular, pulmonary, hepatic or renal condition, which in the opinion of the PI may increase the risk to the subject from participating in the study.
- Any other condition or circumstance that in the opinion of the investigator may pose a threat to the subject.

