### **7.9.6 Dose Discontinuation in Individual Subjects**

Reasons for discontinuation of study vaccine administration in an individual subject include, but are not limited to, the following:

1. Anaphylactic reaction following administration of study vaccine
2. Significant (Grade 3 or 4) reactions following administration of study vaccine (including severe pain, severe swelling, severe headache, persistent high fever or other severe systemic or local reactions) that, in the opinion of the investigator or sponsor, preclude further administration of study vaccine
3. The occurrence of an SAE (See Section 11.5.1) whose relationship to the study vaccine is judged to be possible or probable
4. Receipt of any investigative drug, investigative vaccine or immunosuppressive medication (inhaled or topical corticosteroids are allowed) within 28 days of study vaccine
5. The occurrence of other medical conditions, unrelated to study vaccine, which, in the opinion of the PI, contraindicate administration of study vaccine
6. Moderate or severe unsolicited AEs (clinical events or laboratory tests) that are indicative of new and significant end organ dysfunction

**Table 5: General Toxicity Table** (Modified from the Pediatric ACTG Toxicity Tables; See Ref. 43)

| **Event** | **Grade I** | | **Grade 2** | | **Grade 3** | | | **Grade 4** | |
| --- | --- | --- | --- | --- | --- | --- | --- | --- | --- |
| **Laboratory Values** | | | | | | | | | |
|  | Conventional  Units | SI Units | Conventional Units | SI Units | Conventional Units | SI Units | | Conventional Units | SI Units |
| Hemoglobin | 7.0-7.9 gm/dL | 4.4-4.9 mmol/L | 6.0-6.9 gm/dL | 3.8-4.39 mmol/L | <6.0 gm/dL | <3.8 mmol/L | | CHF 2o to anemia | CHF 2o to anemia |
| Leukocytes | 3.0-3.9 103  per mm3 | 3.0-3.9 109/L | 2.0-2.9 103  per mm3 | 2.9-2.0 109/L | 1.0-1.9 103  per mm3 | 1.9-1.0 109/L | | <1.0 103  per mm3 | <1.0 109/L |
| Platelets | 90,000-109,999 per mm3 | 90.0-109.9 109/L | 75,000-89,999  per mm3 | 75.0-89.9 109/L | 50,000-74,999 per mm3 | 50.0-74.9 109/L | | <50,000 per mm3 | <50.0 109/L |
| Creatinine | 1.1-1.9 mg/dL | 92-176 mol/L | 2.0-3.9 mg/dL | 177-353 mol/L | 4.0-5.9 mg/dL | 354-530 mol/L | | >6.0 mg/dL | >530 mol/L |
| ALT | 45-60 IU/l | 45-60 IU/l | 61-105 IU/l | 61-105 IU/l | 106-147 IU/l | 106-147 IU/l | | > 148 IU/l | > 148 IU/l |
| **Systemic Events** | | | | | | | | | |
| Fever | 37.5-38.0oC | | 38.1-39.0oC | | 39.1-40.5oC | | >40.5o persistent >48 hours | | |

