Parents of subjects will provide a medical history (with special attention to any history of recurrent infections to suggest immune suppression, previous history of splenectomy, and prior vaccine reactions). Subjects will also undergo physical examination and routine standard laboratory screening tests, which include complete blood count (CBC) and serum chemistry profiles (creatinine, ALT). Subjects will be excluded from participation if they meet any of the exclusion criteria (Section 7.5). Subjects excluded from this study because of significant abnormalities will be referred to the local health center for evaluation. All screening tests will be completed within 35 days prior to entry into the study; laboratory tests may be conducted at other times during the course of the trial if judged necessary for the safety of the subject by the investigators. All subjects randomized into the study will be identified and followed by SID number and by name (full name in source documents, but no name or initials in CRFs). All screening and follow-up diagnostic laboratory studies will be performed at the WRP Kombewa Clinic laboratory. Information gathered during screening (medical history, physical examination, and laboratory analysis) will be recorded in the screening source documents.

The investigator will ensure randomization (See also Section 10.3) of 135 eligible subjects who fulfill all the inclusion criteria and none of the exclusion criteria. Subjects in each cohort will be randomized separately from the other cohorts, at the times of first vaccinations. A picture ID of parent and child will be created and given to each parent. Copies of these pictures will also be kept in the source document file. A Case Report Form (CRF) will be filled in for all subjects enrolled in the study. All data collected during the study will be recorded on source documents and transcribed into the CRF by a transcription team trained in this process.

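### The creatinine exclusion limit in Section 7.5 is one limit in two units that do not match: 92.2 (SI) and 1.1 mg/dl

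*Protocol*

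**What the plan says.** Section 7.5 lists criteria that bar entry if any one applies. One reads "Decreased renal function: serum creatinine levels > 92.2", followed by a bracketed equivalent of > 1.1 mg/dl.

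Table 5 in Section 7.9.6 grades creatinine in both units. Grade 1 is "Creatinine | 1.1-1.9 mg/dL | 92-176", Grade 2 is "2.0-3.9 mg/dL | 177-353", Grade 3 is "4.0-5.9 mg/dL | 354-530" and Grade 4 is ">6.0 mg/dL | >530".

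The limit applies to every screened child. Section 8.1.1 includes "serum chemistry profiles (creatinine, ALT") among the routine screening tests. Section 8.2 has the results and the eligibility criteria reviewed again at Visit 2, before randomization. No section names the unit in which the clinic laboratory reports creatinine, or says which of the two figures decides.

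**The concern.** A limit given in two units should exclude the same children whichever is used. Here the SI figure is the stricter one, so between the two figures one sentence of the protocol gives two answers about eligibility.

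At stake is how clearly a mandatory entry criterion is stated. Staff who read a result against the SI figure and staff who read it against the mg/dl figure could reach opposite decisions, each following the text. The same pair, with 92.2 shortened to 92, is the lower edge of Grade 1 creatinine in Table 5.

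In the text available for this review the SI unit is printed as mM/l. It is read here as micromol/l. The micro sign is missing elsewhere in the same text (doses appear in g, Table 5 in mol/L), so the printed unit is not counted as an error. The number is a separate matter: 92 recurs in Table 5, so it is not a garbled character.

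**Working it through.** **Inputs.** The exclusion pair comes from Section 7.5 and the grade bounds from Table 5. The implied factor is the SI figure divided by the mg/dl figure.

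| Bound | mg/dl | micromol/l | Implied factor |
|---|---|---|---|
| Exclusion limit (7.5) | 1.1 | 92.2 | 92.2 / 1.1 = 83.8 |
| Grade 1, lower | 1.1 | 92 | 92 / 1.1 = 83.6 |
| Grade 2, lower | 2.0 | 177 | 177 / 2.0 = 88.5 |
| Grade 3, lower | 4.0 | 354 | 354 / 4.0 = 88.5 |
| Grade 4 | 6.0 | 530 | 530 / 6.0 = 88.3 |

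**Step 1: the protocol's own factor.** The last three pairs agree once the SI figures are treated as rounded to whole numbers:

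- 2.0/177 allows 176.5/2 to 177.5/2 = 88.25 to 88.75
- 4.0/354 allows 353.5/4 to 354.5/4 = 88.375 to 88.625
- 6.0/530 allows 529.5/6 to 530.5/6 = 88.25 to 88.417

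The range common to all three is 88.375 to 88.417, or about 88.4. The upper ends of the grades (1.9/176, 3.9/353, 5.9/530) are not used. Their SI values only run up to the start of the next grade and are not conversions; for example, 1.9 × 88.4 = 168.0, not 176.

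**Step 2: try to reproduce the stated pair.**

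- 1.1 × 88.4 = 97.2 micromol/l, not 92.2.
- 92.2 / 88.4 = 1.04 mg/dl, not 1.1.

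The pair is not reproduced.

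**Step 3: can rounding explain it?**

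- If 1.1 is a rounded value, it covers 1.05 to 1.15 mg/dl, that is 1.05 × 88.4 = 92.8 to 1.15 × 88.4 = 101.7 micromol/l. This range does not contain 92.2.
- In the other direction, 1.04 rounds to 1.0, not 1.1.

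**Step 4: the disputed band.**

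- It runs from above 92.2 up to 97.2 micromol/l, or above 1.04 up to 1.10 mg/dl.
- Its width is 97.2 − 92.2 = 5.0 micromol/l, and 5.0 / 97.2 = 5.1% of the limit.

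**Step 5: mg/dl reported to one decimal.**

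- A result of 1.0 is 88.4 micromol/l, which is eligible on both figures.
- A result of 1.1 is 97.2 micromol/l. It is not above 1.1 mg/dl, so it is eligible on that figure, but it is above 92.2, so it is excluded on the SI figure.
- A result of 1.2 is 1.2 × 88.4 = 106.1 micromol/l, which is excluded on both.

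Only exactly 1.1 is in dispute.

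**Step 6: the Grade 1 edge at the same precision.** A result of 1.0 (88.4) is below 92 and ungraded in both columns. A result of 1.1 (97.2) is Grade 1 in both. Nothing is reclassified. A discrepancy needs mg/dl to two decimals, or a direct SI result read against the mg/dl column.

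**The case against.** The strongest reply accepts the arithmetic and disputes the consequences. Most of it stands.

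- **Unequal treatment.** A reader might infer that similar children will be handled differently. The protocol does not show this. Section 8.1.1 puts all screening and follow-up diagnostic tests in the one Kombewa clinic laboratory, Section 9.1 places the scheduled creatinine tests there, and Section 9.3 puts its assays under SOPs. If that laboratory reports in one unit, which the protocol does not state, one cut-off would probably apply to everyone. What remains is that the text does not say whether that cut-off is 92.2 or 97.2 micromol/l.
- **Grade 1 as a decision threshold.** A reader might also infer that the Table 5 slip affects safety decisions. It does not. In Section 7.9.2 the dose-limiting laboratory rule starts at Grade 2, and discontinuation for laboratory abnormalities needs Grade 4. In Section 7.9.6 individual discontinuation concerns Grade 3 or 4 reactions, or moderate or severe unsolicited events. The Grade 2 to 4 entry points convert correctly. At most the descriptive grading or tabulation of abnormal values (Section 13.5.4) is touched.
- **Bias.** Eligibility is settled before randomization (Section 8.2), and creatinine is not a named endpoint in Sections 13.1 or 13.2. No effect on the randomized comparison is shown.
- **Discretionary exclusions.** Section 7.5 also lets the investigator exclude for a renal or other condition thought to raise risk. That can remove a child in the band, but it does not settle what the numerical limit is.

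The reply does not make the two figures equal, and it points to no place that says which one governs.

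**Conclusion.** The point holds in a limited form. The creatinine exclusion limit is wrong as written, because its two figures cannot both be the limit. On the protocol's own conversion they are 5.0 micromol/l apart, about 5% of the limit. A child above 92.2 and up to 97.2 micromol/l is excluded by one figure and eligible by the other.

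The number of such children cannot be derived from the protocol; few are likely. The Grade 1 lower bound repeats the slip without consequence for any stopping, escalation or dosing rule. This is a small correction to a mandatory criterion. It is not a threat to the trial's safety rules or comparisons.

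The conclusion assumes that the SI unit is micromol/l and that the Grade 2 to 4 entry points in Table 5 show the intended conversion.

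**What to change.** In Section 7.5, reconcile the two figures to one limit, give the other unit as its correct conversion, and state which figure governs eligibility, preferably the one in the unit the clinic laboratory reports. On Table 5's factor the consistent pairs are 92.2 micromol/l with 1.04 mg/dl, or 97.2 micromol/l with 1.1 mg/dl. The protocol does not show which was meant, and the clinical choice is the sponsor's. If mg/dl is reported to one decimal, the limit should be worded so that a result of exactly 1.1 has one outcome. Align the lower bound of Grade 1 creatinine in Table 5 at the same time.

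The cost is two numbers and one sentence naming the governing figure. No design, sample size or analysis changes.
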